## Method and design

### Aim of the study

The overall aim of the study is to evaluate the efficacy of individualized lifestyle intervention compared to the usual care in PCOS women who wish to conceive. We hypothesized that individualized lifestyle intervention improves fertility outcomes in PCOS women who wish to conceive when compared to the usual care. To test the hypothesis, we plan to randomize PCOS women into two groups: group A will receive the intervention which will consist of individualized advice on diet and physical exercise along with a telephonic reminder system and follow-up visits, and group B (control) will receive one-time advice on diet and physical exercise. Both groups will receive up to three cycles of ovulation induction with letrozole after 3 months of randomization during the 6-month treatment period.

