### Inclusion and exclusion

Women attending the fertility clinic will be screened for eligibility. The inclusion criteria will be (i) women aged between 19 and 37 years who have been diagnosed as PCOS by the Rotterdam criteria and wishing to conceive, (ii) body mass index (BMI) ≥ 23 kg/m^2^ but ≤ 35 kg/m^2^ and (iii) duration of infertility ≤ 3 years. The exclusion criteria will be as follows: (i) women planning to take medical treatment at hometown and not available for follow-up period (6 months); (ii) does not have a mobile phone in the house; (iii) pregnancy; (iv) late-onset congenital adrenal hyperplasia (CAH) and androgen secreting tumours; (v) diabetes mellitus, uncontrolled hypothyroidism (TSH > 10 IU/ml), hyperprolactinemia (> 70 ng/ml), bronchial asthma, chronic kidney and liver disease; (vi) prediabetic on metformin or insulin sensitizers or other anti-diabetic medicines; (vii) inflammatory arthritis or any lower limb pathology which precludes exercise; (viii) gastro-intestinal conditions (e.g. ulcerative colitis, Crohn’s disease, coeliac disease) which require special dietary advise; (ix) on anti-psychiatric medications; (x) undiagnosed uterine bleeding; (xi) medical conditions which are contraindications for pregnancy; (xii) previous history of receiving > 6 ovulation induction cycles with letrozole or laparoscopic ovarian drilling; (xiii) previous history of bariatric surgery or planning other strategies for weight loss beyond the trial intervention including but not limited to Fad diets, intra gastric procedures or on weight loss medication; and (xiv) other known causes of infertility which are indications for assisted reproductive technology (ART) treatment, namely severe endometriosis, severe male factor infertility, male partner with azoospermia and documented severe tubal pathology.

Newly detected prediabetics will be included only if they are willing for an initial trial of lifestyle intervention for glycaemic control. We will repeat glycosylated haemoglobin (HbA1c) at 3 months interval, post-randomization, to assess the glycaemic control. If the Hb1Ac is ≥ 6.5%, then initiation of metformin will be considered, and the participant will be followed up as per protocol but will not be considered for per protocol analysis.

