### Dispensing and scheduling of the individualized lifestyle intervention

#### Weeks 0 and 1 (session 1) (for intervention and control arm)

Post-randomization, same day: blood tests (hormonal and metabolic parameters) and anthropometric measurements, including body weight, will be measured. The blood tests will include blood count, serum follicle stimulation hormone (FSH), serum luteinizing hormone (LH), prolactin, thyroid-stimulating hormone (TSH), dehydroepiandrosterone sulphate (DHEAS), 17 hydroxy progesterone, serum testosterone, sex hormone-binding globulin (SHBG), serum insulin, oral glucose tolerance test with 75 g glucose at 0 and 2 h, fasting lipid profile, HbA1c, uric acid and serum adiponectin. The hormonal and other metabolic parameters will be collected at individual sites and sent to a designated central laboratory for analysis. This central accredited laboratory facility will ensure standardization.

A transvaginal ultrasound will be performed and antral follicle counts and ovarian volume (using TVS with a 6.5 to 8.0 MHz probe). The trial staff will then take the anthropometric measurements while the clinician will obtain the ultrasound report. The clinician will also record information on menstrual regularity and pregnancy status. A pregnancy test will be performed if clinically indicated. The trial staff or nurse will record the quality-of-life score using the prespecified tool [22].

In-person introduction of the programme and the need for weight loss. Participants will be given the food and activity questionnaire and reviewed the same day/week over the phone/in person (flexible). Based on the questionnaire, the dietician and physiotherapist will advise individualized diet/exercise for the intervention arm. For the control arm, one-time advise on diet and exercise will be given (Fig. 1).

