### Secondary outcomes

There will be several secondary outcomes which will measure clinical, endocrinological and quality of life parameters and are listed below:(i)Clinical pregnancy rate (time frame: 0 to 9 months post-randomization for participants who conceive within 6 months following randomization): ultrasound evidence of gestational sac or definitive clinical evidence of pregnancy. An ectopic pregnancy will also be considered a clinical pregnancy [24].(ii)Ongoing pregnancy rate (time frame: 0 to 9 months post-randomization for participants who conceive within 6 months following randomization): a viable intrauterine pregnancy as documented by ultrasound after 12 completed weeks of gestation.(iii)Miscarriage rate (time frame: 0 to 12 months post-randomization for participants who conceive within 6 months following randomization): miscarriage is defined as a spontaneous loss of pregnancy before 20 completed weeks of gestational age [23].(iv)Ectopic pregnancy rate (time frame: 0 to 9 months post-randomization for participants who conceive within 6 months following randomization): ectopic pregnancy is defined as pregnancy outside the uterus as diagnosed by ultrasound, surgically or by histopathology [24].(v)Stillbirth: defined as the death of a foetus prior to the complete expulsion or extraction from its mother after 20 completed weeks of gestational age [23].(vi)Time to pregnancy (time frame: 0 to 8 months post-randomization for participants who conceive within 6 months following randomization): from randomization to the documentation of pregnancy (calculated in days).(vii)Positive pregnancy rate (time frame: 0 to 7 months for participants who conceive within 6 months following randomization): defined as positive urine pregnancy test or serum beta human chorionic gonadotrophin (hCG) > 5 IU/ml.(viii)Mean weight loss (time frame: 6 months post-randomization): difference between baseline and follow-up at 6 months).(ix)Improvement in menstrual regularity (time frame: 6 months post-randomization): (according to the International Federation of Gynecology and Obstetrics (FIGO) 2018 guidelines variation of the cycle to be called regular is 7–9 days depending on age. Age 18–25 years ≤ 9 days; age 26–41 years ≤ 7 days is regular); proportion of women in whom regularization of the menstrual cycle is recorded by a total number of women in whom menstrual regularity is recorded.(x)Differences in anthropometric parameters (time frame: 6 months post-randomization) (waist circumference, hip circumference, neck circumference, waist hip ratio, waist height ratio and wrist circumference) at the end of the trial period.(xi)Improvement in hormonal and metabolic parameters (time frame: 6 months post-randomization) [biochemical markers such as lipid profile and glycaemic parameters, visceral adiposity index (VAI) and lipid accumulation product (LAP)] over the baseline.(xii)Quality of life (PCOS specific) assessment (time frame: 6 months post-randomization) [22].(xiii)Pregnancy-related complications (time frame: 0–17 months post-randomization for participants who conceive within 6 months following randomization) (GDM, PIH, preterm birth): obstetric outcomes—gestational diabetes, hypertensive disorder of pregnancy, preterm delivery (< 37 weeks), very preterm birth (< 32 weeks), low birth weight (< 2500 g) or high birth weight (> 4000 g)

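### Secondary outcome (ix), menstrual regularity: the stated denominator includes women already regular at baseline, and the 6-month reading reflects cycles under letrozole, not spontaneous cycles

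*Protocol article*

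**What the plan says.** All references are to the protocol article.

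- **Time point.** Secondary outcomes, item (ix), names the endpoint as "Improvement in menstrual regularity (time frame: 6 months post-randomization". No other time point is given.
- **Criterion.** A cycle is judged by its variation only: "Age 18–25 years ≤ 9 days; age 26–41 years ≤ 7 days is regular". No limit on cycle length or frequency is stated, and there is no rule for women without bleeds.
- **Proportion.** The endpoint is the "proportion of women in whom regularization of the menstrual cycle is recorded by a total number of women in whom menstrual regularity is recorded".
- **Entry.** Inclusion and exclusion admits "women aged between 19 and 37 years who have been diagnosed as PCOS by the Rotterdam criteria and wishing to conceive", with BMI and duration-of-infertility limits. Irregular cycles are not listed as a requirement.
- **Baseline record.** At session 1 (weeks 0 and 1), in both arms, "The clinician will also record information on menstrual regularity and pregnancy status".
- **Concurrent treatment.** Aim of the study: "Both groups will receive up to three cycles of ovulation induction with letrozole after 3 months of randomization during the 6-month treatment period". The section on medical treatment after 3 months makes the number of cycles depend on unit policy, and the week 26 section says treatment can begin after 12 weeks if the woman has not conceived.
- **Visits.** The week 13 session is for the intervention arm only and does not list menstrual regularity among its checks. The Control section plans the control arm's review at 6 months.

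**The concern.** The endpoint is described as an improvement, but three parts of its definition work against that.

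1. The denominator is everyone with a regularity record. A woman regular at entry cannot be regularised, yet on the literal wording she is counted. The Statistical analysis section reports categorical endpoints as a difference in proportions, and that is the measure this dilutes.
2. Variation alone does not separate regular cycles from infrequent but evenly spaced ones. The Background names anovulation and oligo-ovulation as the route to infertility in PCOS, so infrequent cycles are relevant here.
3. Women who have not conceived may have up to three letrozole cycles in either arm before the reading, and nothing excludes induced cycles from scoring.

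The text also leaves open how women pregnant at 6 months are counted. They have no current cycle, and the intervention is meant to change how many there are.

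At stake is the interpretation of one secondary outcome. The Discussion lists menstrual symptoms among the domains that the trial will capture, and a reader could take this result as the effect of lifestyle advice on natural cycles.

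**Working it through.** **The plan's own figure (context only).** The article gives no rate or power for this endpoint. Its sample size, for live birth at 30% v 40%, two-sided alpha 0.05 and 90% power, reproduces with the unpooled formula: (0.30×0.70 + 0.40×0.60) × (1.960 + 1.282)² / 0.10² = 473 per arm. Then 946 / 0.80 = 1183. It is not in dispute.

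**Assumptions for the illustration.** Women per arm with a record: 600 × 0.80 = 480 (planned size less the planned 20% attrition). Regularised among women irregular at baseline: 30% v 40%. Share irregular at baseline, s: 50% to 100%. None of the menstrual rates comes from the article.

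**Step 1: denominator.** If already-regular women never count as regularised, each arm's proportion is s × p. If instead 95% of them are counted as regular, it is 0.95(1 − s) + s × p. The difference is s × 10 points either way. Power is Φ{[Δ − 1.96√(2p̄(1−p̄)/n)] / √([p₁(1−p₁) + p₂(1−p₂)]/n)}, with n = 480 for all recorded women and n = 480s for irregular women only.

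| Irregular at baseline | Difference, all recorded | Power, regular women never count | Power, 95% of them count | Power, irregular women only (10 points) |
|---|---|---|---|---|
| 100% | 10 | 90% | 90% | 90% |
| 90% | 9 | 85% | 81% | 87% |
| 80% | 8 | 79% | 70% | 83% |
| 70% | 7 | 71% | 58% | 78% |
| 60% | 6 | 63% | 47% | 71% |
| 50% | 5 | 53% | 37% | 63% |

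Worked line at 80%, never counted: 24% v 32%, p̄ = 0.28, giving (0.08 − 1.96 × 0.02898) / 0.02887 = 0.80 and power 79%. Irregular women only: n = 384, giving (0.10 − 1.96 × 0.03442) / 0.03423 = 0.95 and power 83%. With 300 recorded per arm the ordering is the same: 59% or 50% against 63%.

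**Step 2: criterion.** Cycles of 60 and 62 days differ by 2 days, inside both age limits, and total 122 days, which fits within 26 × 7 = 182 days. Such a woman passes the stated rule. They do not fit within the first 13 weeks (91 days), so the case arises mainly where letrozole is started late or not given.

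**Step 3: letrozole.** Suppose it makes a fraction m of women look regular whatever their arm, so that p becomes m + (1 − m)p.

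| m | Control v intervention | Difference | Power, 480 per arm |
|---|---|---|---|
| 0 | 30% v 40% | 10 | 90% |
| 25% | 47.5% v 55% | 7.5 | 64% |
| 50% | 65% v 70% | 5 | 38% |
| 75% | 82.5% v 85% | 2.5 | 18% |

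**Step 4: conception.** The primary outcome counts only births from conceptions within 6 months. At the planning rates, nearly all of those women would be pregnant at the reading. If they have no regularity record, at most 600 × 0.70 = 420 control and 600 × 0.60 = 360 intervention women remain. The two groups would then be selected by an outcome that arises after randomisation.

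**The case against.** The strongest reply is that the trial compares lifestyle intervention with usual care when letrozole is available to both arms. Regularity at 6 months then answers a fair question about lifestyle advice in that setting. This stands. A reader might infer that the endpoint cannot show any lifestyle effect, or that neither a null nor a positive result could be read. The documents do not support that: baseline-regular women and arm-independent masking mainly dilute the difference, and letrozole exposure will vary with unit policy. What the reading cannot isolate is the effect on spontaneous cycles.

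A reader might also infer that women with no bleed drop out of the denominator. No section says so. The denominator is women with regularity recorded, and a clinician could record a woman without bleeds as not regular. The text is silent, which calls for a rule but does not prove an exclusion.

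The criterion point should not be overstated either. Three cycles of 60, 62 and 65 days total 187 days and do not fit into 182. Two such cycles do.

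The denominator wording is loose. Regularization suggests a change from irregular, and analysis-set detail is often left to the analysis plan. But the article states a denominator, and its literal reading is all recorded women.

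Moving the reading before letrozole is a trade-off, not a clear gain. The week 13 visit is for the intervention arm only, about 12 weeks yields few cycles, and half of the lifestyle period would be ignored.

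**Conclusion.** The point holds in limited form. Item (ix), read literally, shrinks any true difference by the share of women irregular at baseline. In the illustration, 10 points become 9 to 5 points at 90% to 50% irregular. Restricting to irregular women at 80% takes the difference from 8 back to 10 points and power from about 79% (or 70%, depending on how regular women are scored) to 83%. These sizes rest on assumed rates of 30% v 40% and 480 women per arm.

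The variation-only criterion can pass long, even cycles. The 6-month reading estimates regularity with lifestyle advice on top of ovulation induction. It is probably attenuated, with a size that depends on an unknown masking fraction and on that fraction being similar in the two arms. It does not measure restoration of spontaneous cycles.

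This is one of thirteen secondary outcomes. The primary outcome and the sample size are unaffected.

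**What to change.** Reword item (ix) as follows.

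- **(a) Denominator.** Use randomised women with irregular or absent cycles at baseline, taken from the session 1 record. That session follows randomisation on the same day in an open-label trial, so the form should state that the record describes cycles before randomisation. A subset fixed by pre-randomisation status keeps the randomised comparison intact.
- **(b) Counting rules.** Count non-pregnant women with no bleed or one bleed as not regular. State one rule, the same in both arms, for women who conceive, so that membership of the denominator does not depend on conception.
- **(c) Interpretation.** Report the 6-month result as regularity under ovulation induction, not as a lifestyle effect on spontaneous cycles.

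Two additions are optional. One is a cycle-frequency criterion written out in the protocol, since the article gives only the variation limits. The other is a supportive analysis of bleed dates before induction in both arms. That would need a way to collect them from controls, who have no week 13 trial visit, and the shorter window yields few cycles.

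The required changes cost protocol wording and a clear baseline field. The downside is a smaller denominator, for example 384 instead of 480 per arm at 80% irregular.

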### Primary outcome

The primary outcome for the trial will be the live birth following conception during the intervention period (time frame: 0 to 16 months post-randomization for participants who conceive within 6 months following randomization). A live birth is defined as the delivery of a live foetus after 20 weeks of gestation [23]. The twins and higher births will be considered as a single live birth event. The denominator for primary analysis will be per woman.

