### Sample size calculation

No previous data is available on live birth following individualized lifestyle intervention in PCOS women who wish to conceive. From previous study performed in one of the trial sites, the live birth rate following usual care which consisted of one-time lifestyle advise and ovulation induction with Letrozole for up to five treatment cycles, was reported as 30% [25]. Due to uncertainty about the likely event rate (live birth rate) in the intervention arm, it was assumed that to convince the clinicians and patients to adopt a change in practice, a modest improvement of 10% in live birth would be required.

For alpha error set at 0.05 and power being 90%, to detect a clinically relevant difference of 10% in the live birth rate following individualized lifestyle intervention, the calculated sample size will be 473 in each arm (total sample size 946). Assuming an attrition of 20%, the total sample size was 1183. We rounded off the total sample size to 1200 with 600 in each arm. With 5 centres participating in the study each site shall recruit 240 subjects each.

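### The menstrual-regularity outcome counts only women with regularity recorded at 6 months, so its denominator depends on who has conceived and the comparison is no longer between the randomised groups

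*Protocol article*

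**What the plan says.** The protocol article, Secondary outcomes, item (ix), sets the endpoint and its timing: "Improvement in menstrual regularity (time frame: 6 months post-randomization". Regularity is judged by variation in cycle length, with limits that depend on age: "Age 18–25 years ≤ 9 days; age 26–41 years ≤ 7 days is regular". The measure is then the "proportion of women in whom regularization of the menstrual cycle is recorded by a total number of women in whom menstrual regularity is recorded". So the denominator is a recording status at follow-up, not the randomised group.

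Other sections bear on this:

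- **Primary outcome:** the trial counts "live birth following conception during the intervention period", that is, conceptions within 6 months of randomisation.
- **Aim of the study:** both arms may receive up to three letrozole cycles in months 3 to 6 of the same window.
- **Statistical analysis:** all randomised women enter the intention-to-treat analysis, which covers primary and secondary endpoints. The only rule for an unknown outcome concerns live birth.
- **Dispensing and scheduling:** menstrual regularity is recorded at the first session. The week 26 list does not mention it and does not say which cycles are to be used for a woman who has conceived.

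**The concern.** A criterion based on cycle variation needs observed cycles. A woman who is pregnant at 6 months has none at that time, so under the stated definition she would largely fall out of both numerator and denominator. Conception in this window is what the intervention is meant to increase. If it works, more women leave the intervention arm than the control arm, and those who remain have been selected after randomisation by something the treatment affects.

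Randomisation then no longer protects the comparison. The article names improvement in menstrual symptoms among the clinical domains it wants to capture, so readers will use this result.

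**Working it through.** **1. The plan's own figures.** The article gives no figure for outcome (ix). Its sample size uses 30% live birth under usual care and says "a modest improvement of 10% in live birth would be required", with alpha 0.05 and 90% power. Reading 10% as percentage points and alpha as two-sided, the unpooled normal formula gives

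n = (1.960 + 1.282)² × (0.3×0.7 + 0.4×0.6) / 0.1² = 472.8, so 473 per arm and 946 in total.

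With 20% attrition, 946 / 0.8 = 1182.5, so 1183. These match the article, which rounds up to 600 per arm. The planning rates are therefore 30% and 40%.

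**2. How many women could leave the denominator.** The documents give no pregnancy rate at 6 months. I use the planning live-birth rates as a stand-in.

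- Control: 600 × 0.30 = 180 leave, 420 remain.
- Intervention: 600 × 0.40 = 240 leave, 360 remain.
- After 20% attrition (480 per arm): 336 and 288 remain.

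The stand-in could be off in either direction. Live births are fewer than conceptions. On the other hand, some pregnancies will have ended by 6 months, and the 30% came from up to five letrozole cycles, against at most three here.

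**3. What this does to the recorded difference.** Let R be the true share regularised in the whole arm, p the share pregnant, and q the share of pregnant women who had regularised. The recorded proportion among non-pregnant women is

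(R − p×q) / (1 − p).

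R and q are assumptions, since the documents give neither. With p = 0.30 and 0.40:

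| True R, control / intervention | q, control / intervention | Recorded, control | Recorded, intervention | Difference (points) |
|---|---|---|---|---|
| 50% / 60% | 1.0 / 1.0 | 28.6% | 33.3% | +4.8 |
| 50% / 60% | 0.9 / 0.9 | 32.9% | 40.0% | +7.1 |
| 50% / 60% | 0.75 / 0.75 | 39.3% | 50.0% | +10.7 |
| 50% / 60% | 0.6 / 0.6 | 45.7% | 60.0% | +14.3 |
| 50% / 60% | 0.6 / 0.9 | 45.7% | 40.0% | −5.7 |
| 50% / 60% | 0.9 / 0.6 | 32.9% | 60.0% | +27.1 |
| 50% / 50% | 0.9 / 0.9 | 32.9% | 23.3% | −9.5 |
| 50% / 50% | 1.0 / 1.0 | 28.6% | 16.7% | −11.9 |

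For example, the first row is (0.50 − 0.30)/0.70 = 0.286 and (0.60 − 0.40)/0.60 = 0.333. A true gain of 10 points can be recorded as smaller, larger or reversed. With no true effect, the rule can produce an apparent harm.

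**4. A case with little distortion.** Suppose the chance of pregnancy depends only on regularity, in the same way in both arms, for example 40% if regular and 20% if not. With true R of 50% and 60%, the recorded rates are 42.9% and 52.9% (+10.1 points), and the odds ratio stays at 1.50. Over the four pairs of pregnancy chances tried, the difference was +9.7 to +10.1 points. In these cases, however, pregnancy differs between arms by at most 4 points (30% against 34%). A 10-point gap in pregnancy, as in step 2, would need a route to conception other than regularity, and that is when the distortion in step 3 arises.

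**The case against.** **The exclusion is inferred.** The article does not say that women who conceive go unscored. A clinician could record regularity from the cycles before conception, and an article may leave such detail to the full protocol or analysis plan. This stands as a caution. But the denominator itself is stated, not left open. As worded it turns on whether regularity was recorded at 6 months, and nothing in the article directs staff to pre-conception cycles. In an open-label trial at five sites, practice could differ.

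**The direction of bias is not fixed.** A reader might infer that the rule removes successes from the better arm and so biases the result towards no effect. The documents do not support that. Conception shows ovulation, not a cycle variation within 7 or 9 days. Letrozole is given in both arms, so a woman can conceive on an induced cycle while her own cycles stay irregular, and removing her removes a non-success. The table shows dilution only when nearly all pregnant women had regularised.

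**Claims of lost power do not stand.** A reader might score success as regular or conceived, assume 60% against 70%, and note that the rates among non-pregnant women become (0.60 − 0.30)/0.70 = 42.9% and (0.70 − 0.40)/0.60 = 50.0%, an apparent loss from 10 to 7.1 points. But the article does not define that composite. Subtracting pregnancy leaves 30% regular and not pregnant in each arm, so the whole 10 points is pregnancy. This does not measure power lost for menstrual regularity.

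**A composite would change the question.** Counting conception as success overlaps with the pregnancy outcomes already listed. This is a fair reason not to impose it as the only definition.

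**Conclusion.** The concern holds in this form. As written, outcome (ix) conditions on a status that arises after randomisation and is tied to the trial's target outcome. It is therefore not a comparison of the randomised groups, and it conflicts with the all-randomised rule in the statistical analysis section.

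On the planning rates, about 180 against 240 of 600 women per arm could drop out of the denominator. This assumes that live birth stands in for pregnancy and that pregnant women go unscored. The effect on the result may be dilution, inflation or reversal: −5.7 to +27.1 points recorded for a true +10 under the assumptions shown, and close to no distortion in the case in step 4. The direction cannot be settled from the document.

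This is one of thirteen listed secondary outcomes. The primary outcome is analysed per woman, and neither it nor the sample size is affected. The definition should be corrected, but it does not threaten the trial's main conclusion.

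**What to change.** Redefine outcome (ix) on all randomised women with known 6-month status, and show by arm the shares who (a) have regular cycles and are not pregnant, (b) conceived within 6 months of randomisation, and (c) have irregular cycles.

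Prespecify one handling of conceivers for the between-arm test. Two workable options are:

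- success is a regular cycle by the stated criterion or conception within 6 months, with the components shown separately; or
- regularity is judged over the last recorded cycles before conception.

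Label the rate among women not pregnant at 6 months as descriptive.

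The cost is a sentence or two in the outcome definition and no extra visits. Conception status is already collected, so the first option needs no new data. Its small drawback is overlap with the pregnancy outcomes, which is why the components are shown. The second keeps the menstrual construct, but it depends on cycle dates being recorded up to conception, which the article does not describe.
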